We will evaluate subjects´ knowledge on insulin therapy using a Web-based questionnaire, containing 10-20 multiple choice questions. The questions will be clinical vignettes of diabetic patients who require initiation and/or adjustment of insulin. For each question, the participant should choose the best option for achieving a better glycemic control, according to current guidelines [1,29-31. Questions regarding insulin therapy will be selected from the American Diabetes Association Self-Assessment Program, Module 2 (Pharmacological Treatment of Hyperglycemia) [35], translated to Portuguese, and adapted to be compatible with the game´s clinical scenarios and learning objectives. Participants´ attitudes regarding diabetes will also be assessed, by the application of Web-based Diabetes Attitudes Scale, version 3 (DAS-3) [36]. The questionnaire and the DAS-3 will be answered by the participants at 3 time points: before the intervention (pre-test), immediately after the intervention (after-test), and 6 months after the intervention (late-test). The average number of right answers will be presented and compared in the different time points within each group (intragroup) using analysis of variance (ANOVA), and between the 2 groups at each time point (intergroup) using Student´s *t* test. A bicaudal significance level of 0.05 will be adopted. Data analysis will be done by intention-to-treat, with last observation carried forward, which means that all randomized participants´ data will be included in the final analysis.

The participants will be asked a few Likert-scale and free text questions at the end of each intervention to assess their general impressions about the intervention (mostly to assess if it was pleasant or enjoyable). Software-recorded data on player´s usage of the game will be analyzed to assess the number of logins, time spent on the game, etc. For the participants in Group A that do not finish the game, the reasons for early withdrawal will be collected by an online questionnaire. We will contact (by phone or email) the participants who do not eventually fulfill the questionnaires at least twice.

In order to detect a minimum standard deviation of 0.5 on the average of right answers with 80% of statistical power at 5% of significance level, we will need to include 128 subjects in our study (64 in each group). We will enroll 160 subjects (80 in each group), in order to compensate for an expected 25% dropout rate.

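### The between-group t test leaves the pre-test score unused; ANCOVA on it would gain precision at no data cost, though it offsets the dropout shortfall only if the pre/post correlation is about 0.25 or more

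*Protocol article*

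**What the plan says.** All of this is in the protocol article, Methods, Educational Efficacy Assessment.

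- **Measurement.** The knowledge questionnaire and the DAS-3 are each completed three times: "before the intervention (pre-test), immediately after the intervention (after-test), and 6 months after the intervention (late-test").
- **Comparison.** Within each group, the time points are compared by ANOVA. The arms are compared "between the 2 groups at each time point (intergroup) using" Student's t test. No between-group analysis uses the pre-test as a covariate; it enters the arm comparison only as a t test of its own.
- **Error rate.** "A bicaudal significance level of 0.05 will be adopted".
- **Sample size.** The target is worded thus: "In order to detect a minimum standard deviation of 0.5 on the average of right answers". Power is set at 80% and alpha at 5%, and the article concludes that 64 per group, 128 in all, are required. Enrolment is then raised: "We will enroll 160 subjects (80 in each group), in order to compensate for an expected 25% dropout rate".
- **Missing data.** "Data analysis will be done by intention-to-treat, with last observation carried forward", so that every randomised participant is analysed.

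The article gives no correlation between pre-test and later scores.

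**The concern.** The article names the between-group test, so this is a stated choice and not a detail left to a fuller document. The choice discards information that the trial will collect anyway. A physician's insulin knowledge before teaching probably predicts part of the score afterwards. An unadjusted t test leaves that part in the error variance, and the within-group ANOVA does not recover it because it does not estimate the difference between arms.

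Two things are at stake. The first is power, in a trial whose enrolment target already falls short of its own dropout assumption. The second is chance imbalance: allocation is by a random number generator with no stratification mentioned, so the arms may differ in prior knowledge, and part of that difference would reappear in the after-test and late-test contrasts. The planned t test at pre-test does not remedy this. If randomisation is sound, any difference it finds is due to chance, and it corrects nothing.

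**Working it through.** **Inputs from the article.** Two-sided alpha 0.05; power 80%; 64 per group; 160 enrolled (80 per group); 25% dropout. The phrase about a minimum standard deviation of 0.5 is read as a standardised difference d = 0.5, which reproduces the stated 64.

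**Assumed.** The correlation r between pre-test and later score, shown from 0.1 to 0.6. The SD of the score is taken as the same in both arms.

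**Step 1: the plan's own figure.** For a two-sample t test with d = 0.5, the noncentral t distribution gives 63.77 per group, hence 64 and 128 in total. Power at 64 is 80.1%. The 128 reproduces.

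**Step 2: dropout.** 160 = 128 × 1.25. Losing 25% of 160 leaves 160 × 0.75 = 120, or 60 per group, which is 8 short of 128. Enrolment that leaves 128 is 128 / 0.75 = 170.7, so 171 (172 with equal arms). Unadjusted power at 60 per group is 77.5%.

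**Step 3: effect of adjustment.** ANCOVA multiplies the error variance by 1 − r², so the effective standardised difference is 0.5 / √(1 − r²). Power comes from the noncentral t distribution with noncentrality [0.5 / √(1 − r²)] × √(n/2) and 2n − 3 degrees of freedom, one being spent on the covariate.

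| r | 1 − r² | Effective d | Power, 64 observed per group | Power, 60 observed per group |
|---|---|---|---|---|
| unadjusted t test | 1 | 0.500 | 80.1% | 77.5% |
| 0.1 | 0.99 | 0.503 | 80.5% | 77.9% |
| 0.2 | 0.96 | 0.510 | 81.7% | 79.2% |
| 0.3 | 0.91 | 0.524 | 83.7% | 81.3% |
| 0.5 | 0.75 | 0.577 | 90.0% | 88.0% |
| 0.6 | 0.64 | 0.625 | 93.9% | 92.4% |

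**Step 4: break-even.** Adjustment makes 120 observed participants worth 128 unadjusted ones when 1 − r² = 120/128 = 0.9375, that is r = √0.0625 = 0.25. Power at 60 per group is then 80.1%.

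**Step 5: chance imbalance.** With 64 per group, 95% of chance differences in mean pre-test score lie within ±1.96 × √(2/64) = ±0.35 SD. With equal SDs at the two time points, about r times the imbalance is expected in the later difference. At r = 0.5, an imbalance at that limit carries over as about 0.17 SD, roughly one third of the 0.5 SD target.

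**The case against.** The strongest reply is that nothing here is wrong. Under randomisation the t test is unbiased and keeps its 5% error rate, its standard error already allows for chance imbalance, and 64 per group is exactly what that test needs. All of this stands. The loss is one of efficiency, not validity.

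Three stronger readings are tempting, and the article does not support them.

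- **A reader might infer that adjustment makes up the enrolment shortfall whatever the data look like.** It does so only at r of about 0.25 or more; at 0.1 or 0.2, power with 60 per group stays under 80%. No r is given. A test of 10 to 20 items, scored after both arms have been taught and again at 6 months, could correlate only weakly with the pre-test.
- **A reader might infer that a pre-test imbalance passes in full into the later differences.** Only about r times its size is expected to.
- **A reader might take 60 per group as the plan's analysis set.** The plan nominally analyses all 160 by last observation carried forward, and a t test on 80 genuine outcomes per group would have about 88% power. But a carried-forward value does not restore the lost outcome. For a participant with only a pre-test, the outcome would be the pre-test score itself and would equal the covariate. The 60 is therefore a count of observed outcomes.

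It can also be said that the dropout inflation is a separate error, present whichever test is used. That is correct: ANCOVA may offset it but does not repair it.

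**Conclusion.** The point holds as an improvement that needs no new data. The named between-group analysis is valid but gives up precision that the planned pre-test would supply for one degree of freedom. On observed outcomes and d = 0.5, the gain with 64 per group runs from 0.4 percentage points of power at r = 0.1 (80.5 − 80.1) to 13.8 at r = 0.6 (93.9 − 80.1). The gain is negligible at low correlation and substantial from about 0.5. Whether it also covers the loss from 80.1% to 77.5% caused by enrolling 160 and not 171 depends on r reaching about 0.25, which the article gives no means of judging. The figures assume equal SDs in the two arms and complete observed scores at the time point concerned.

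**What to change.** - Compare after-test and late-test knowledge scores by ANCOVA on arm with the pre-test score as covariate. Report the adjusted mean difference with its 95% CI at each time point.
- Do the same for the DAS-3, with its own pre-test as covariate.
- Show pre-test scores by arm descriptively and drop the significance test at that time point.
- Fit the ANCOVA to observed after-test and late-test scores, not to carried-forward values, and reconcile this with the present statement that all randomised participants are analysed by last observation carried forward.
- State that the pre-test is completed before allocation is revealed. The article randomises at study entry in an unblinded trial and places the pre-test only before the intervention, so the order is open. A covariate measured after participants know their arm could be affected by it.
- Do not rely on the adjustment to cover dropout unless r of at least about 0.25 can be supported. Otherwise enrol 171 to 172.

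The cost of the analysis change is wording and one degree of freedom, since the pre-test is already scheduled. Fixing the order of pre-test and allocation is a small procedural change. Only the last item, if needed, adds participants: 11 to 12.

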## Introduction

Achieving and maintaining good glycemic control is the mainstay of treatment of diabetes mellitus (DM) [1]. Unfortunately, only 24-56% of patients with DM are within the goal of the glycated hemoglobin A1c <7%, in most countries [2,3].

Worldwide, according with public health trends, most diabetics are treated by primary care physicians (PCPs) [4], but these professionals lack knowledge and confidence on several aspects of DM management [5], specially regarding insulin use [6]. This contributes to the common problem known as clinical inertia, "the failure to advance therapy when indicated" [7], underuse of insulin [8], and poor glycemic control.

Continuing medical education (CME) on DM and insulin is often advocated as a solution to optimize the knowledge and the practice of PCPs [9]; however, traditional CME activities (such as lectures and group discussions) have small and short-lasting efficacy [10]. Thus, new educational methods are urgently required.

Digital games are currently one of the six greatest trends in higher education [11], since they are able to "create a tight marriage among content, game play, and valued ways of thinking and acting" [12]. One of the reasons for increasing interest in games for higher and professional education is the huge familiarity of most college students with the medium [13]. Most medical students, for instance, even those who do not play video games, have highly favorable views about the use of video games and new technologies in medical education [14]. However, the most compelling reason for adopting learning games, probably, is their pedagogical adequacy. Good learning games are usually built by the same rules that guide the design of effective learning activities, which include stimulus to players´ intrinsic motivation, practice and repetition, effective feedback, arousal of positive feelings, intensity of the experience, and learner choice/involvement [15]. In the medical area particularly, the use of games and simulators for learning clinical skills has the additional advantage of increasing the safety of real patients [16].

In the field of diabetes, some games for education of patients [17-19], and a few technology-based initiatives for education of health professionals [10,19-25] have been described, but to our knowledge, no game have been reported for education of health professionals on diabetes or insulin.

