### Educational Efficacy Assessment

After final adjustments in the game, guided by usability and playability assessments, the efficacy of InsuOnline as an educational tool will be assessed in an unblinded randomized controlled trial [34]. We will send a letter of invitation to all primary care physicians (PCPs) who work in Londrina to participate in the study. If those PCPs do not fulfill our sample size, we will also invite PCPs from other cities in the state of Paraná (Brazil), such as Maringá, Curitiba, or São José dos Pinhais. The PCPs who are willing to participate in the study will be included and randomized at study entry, using a random number generator, to 1 of 2 groups. We will exclude clinical endocrinologists or diabetologists.

Physicians enrolled in the Group A will be exposed to InsuOnline. They will be asked to play the game until its end, on the Web (with an individual login) in their own time and rhythm. Physicians enrolled in the Group B will undertake a traditional instructional session, during one afternoon, composed of a short lecture and a group discussion of clinical cases, which will be identical to the ones included in InsuOnline. This traditional instructional session will focus on the same teaching topics of the game, and it will be coordinated by a clinical endocrinologist not linked to the research team in order to avoid potential biases. This endocrinologist will be trained by the researcher endocrinologists, and he will use didactic material prepared by our team.

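### Last observation carried forward as the only missing-data rule assumes no learning or no forgetting, and can distort the between-arm comparison to a degree that depends on unstated dropout timing

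*Protocol article*

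**What the plan says.** All of this is in the protocol article, under Educational Efficacy Assessment unless noted.

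- Knowledge and attitudes are measured three times: before the intervention, immediately after it, and 6 months later. The arms are compared by t test at each time point. "A bicaudal significance level of 0.05 will be adopted".
- Missing scores: "Data analysis will be done by intention-to-treat, with last observation carried forward". The article takes this to mean that every randomised participant enters the final analysis.
- Sample size: the trial is to "detect a minimum standard deviation of 0.5 on the average of right answers" "with 80% of statistical power at 5% of significance level", and for this "we will need to include 128 subjects in our study (64 in each group". To cover an expected 25% dropout, "We will enroll 160 subjects (80 in each group".
- Entry: "The PCPs who are willing to participate in the study will be included and randomized at study entry". The pre-test is placed before the intervention, but its order relative to allocation is not given.
- Introduction: "traditional CME activities (such as lectures and group discussions) have small and short-lasting efficacy". The comparator arm receives a short lecture and a group discussion.
- Non-responders will be contacted at least twice, and reasons will be collected from Group A physicians who do not finish the game.

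**The concern.** Knowledge scores are expected to rise after teaching and then, at least in the lecture arm, to fall back. Carrying the last score forward contradicts both movements. The only score before the after-test is the pre-test, so a physician who was taught but did not answer is recorded as having learned nothing. The only score between that and the 6-month test is the after-test, so a physician who answered once and was then lost is recorded as having kept everything. One who misses both tests carries the pre-test to 6 months.

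Three consequences follow.

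- The sample size and the analysis do not match. Extra enrolment replaces lost subjects; it does not restore a mean difference diluted by filled-in scores.
- The arms offer different ways to drop out (an unfinished self-paced web game, a missed afternoon). Unequal loss would turn the rule into a bias, in a direction that depends on which arm loses more.
- At 6 months the rule hides decay, which is what that measurement is there to show, and so favours whichever arm decays more.

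**Working it through.** **Inputs from the article:** 64 per arm needed, 80 per arm enrolled, two-sided 5%, 80% power, 25% dropout, and a difference of 0.5, read as 0.5 SD.

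**Assumptions, not in the article:** within-arm SD of 1 at each time point; equal pre-test means, set to 0; after-test gain g in the lecture arm and g + 0.5 in the game arm; a share m of each arm misses the after-test, unrelated to score; those who miss it were taught and would have gained like the others.

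**1. The plan's own figure.** With 64 per arm and 0.5 SD, the noncentral t distribution gives 80.1% power. The stated 64 per arm reproduces.

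**2. Completers only at 25% dropout.** 80 × 0.75 = 60 per arm, which gives 77.5% power at 0.5 SD. This, rather than 80%, is the fair comparator. The small shortfall comes from the dropout inflation and is a separate matter.

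**3. After-test under the carried-forward rule, equal loss.**

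- Mean difference = (1 − m) × 0.5. At m = 0.25 this is 0.75 × 0.5 = 0.375.
- Variance in an arm with gain G = 1 + m(1 − m)G², because the arm is now a mixture of taught and untaught scores.
- Example, m = 0.25 and g = 1.0: the variances are 1 + 0.1875 × 1.5² = 1.422 (game) and 1 + 0.1875 × 1.0² = 1.188 (lecture). The standard error is √((1.422 + 1.188)/80) = 0.181, the noncentrality is 0.375/0.181 = 2.08, and power is 54%.

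| Missing after-test, each arm | Mean difference (SD) | Power, g = 0 | g = 0.5 | g = 1.0 |
|---|---|---|---|---|
| 5% | 0.475 | 85% | 84% | 82% |
| 10% | 0.450 | 80% | 79% | 75% |
| 15% | 0.425 | 76% | 73% | 68% |
| 25% | 0.375 | 64% | 61% | 54% |

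**4. After-test, no true difference, unequal loss.** If both arms gain g, the false difference (game minus lecture) is (m_lecture − m_game) × g. With an assumed 35% missing in the game arm and 15% in the lecture arm:

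- g = 0.2: −0.20 × 0.2 = −0.04 SD, rejection rate 5.7%
- g = 0.5: −0.10 SD, rejection rate 9.4%
- g = 1.0: −0.20 SD, rejection rate 21.2%

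With 30% against 20%, the rates are 5.2%, 6.1% and 8.9%. The reverse split gives the same bias with the opposite sign. With equal loss and equal gains the rate stays at 5%.

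**5. Late-test, true 6-month difference 0.5 SD (game 1.0, lecture 0.5), with 25% of each arm lost only after the after-test.**

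- Equal decay (after-test 1.5 and 1.0): the carried-forward means are 0.25 × 1.5 + 0.75 × 1.0 = 1.125 and 0.25 × 1.0 + 0.75 × 0.5 = 0.625. The difference stays 0.5 and power is about 87%.
- Decay in the lecture arm only (after-test 1.0 in both): the means are 1.0 and 0.625. The difference falls to 0.375 and power to 64%.

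**The case against.** The strongest reply is that the damage depends on facts that the article does not give. One 25% figure covers a trial with a 6-month visit, and much of the loss may fall after the after-test. Few physicians may miss a test given straight after the teaching, and the planned contacts would help. A reader might infer that the rule removes the stated power. The text does not support that: 5% missing keeps power above 80%, and loss that falls only after the after-test with equal decay leaves about 87% at 6 months. This stands, and it is why the result is a range.

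A second reply also stands in part. Physicians who never attended or barely played may truly have gained little. For them the pre-test score is near the truth, and a diluted difference is close to the real effect of assignment. The distortion is clearest in those who were taught and did not answer. It also follows that a missing-at-random model is not neutral: it credits non-participants with the learning of similar participants and could flatter the game.

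Third, the 21% rejection rate needs both a marked imbalance and a 1 SD gain in the lecture arm, although the Introduction calls such gains small as well as short-lived. It is the severe end of the range.

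Two further inferences are not supported. A reader might conclude that physicians lost before the pre-test cannot be included because allocation comes first, but the article does not give that order. A reader might also say that the standard errors of the t test are wrong. Each physician contributes one value per time point, no such error has been shown for the between-arm comparison, and nothing here relies on it.

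None of this supports carrying forward as the only rule. If the lecture arm decays more, the rule works against the game at 6 months, but that is still a wrong estimate of retention.

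**Conclusion.** The concern holds in limited form, as a should-fix. The article fixes one missing-data rule, and that rule contradicts its own expectation that the effect of traditional teaching fades. It also does not match a sample size that counts dropouts as lost.

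Under the assumptions listed, after-test power with 80 per arm runs from 82-85% at 5% missing to 54-64% if the whole planned 25% miss that test. The latter compares with 77.5% from 60 completers per arm. Under no true difference, the 5% test keeps its level with equal loss and equal gains, and rejects about 6% to 21% of the time with 35% against 15% missing. At 6 months the rule leaves the difference intact if both arms decay equally and shrinks it if only the lecture arm does.

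Where the truth lies depends on when and in which arm physicians drop out, whether they had been taught, and how large the gains are. The article states none of these.

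**What to change.** - **Main analysis.** Replace carrying forward with a likelihood-based repeated-measures mixed model on all observed scores (pre-test, arm, visit, arm by visit, unstructured covariance), or with multiple imputation by arm.
- **Sensitivity analysis.** Add one reference-based or delta-adjusted analysis in which physicians who did not take the intervention gain little or nothing. It is needed because the main model credits them with the learning of similar participants.
- **Pre-test.** State that it is completed before allocation is disclosed, so that every randomised physician has a baseline score and can be included.

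The cost is a change of wording in the analysis section, slightly more analysis work, and reliance on a missing-at-random assumption, which the sensitivity analysis tests. The game is still in its alpha version, so the change can be made before any trial data exist.

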## Methods

### Game Design

A multidisciplinary team was assembled, consisting of clinical endocrinologists ([name], [name]), experts in medical education ([name], [name], [name]) and software developers/game designers ([name], [name]). The endocrinologists compiled a list of main topics on insulin initiation and adjustment for treatment of adults with DM, in the context of a primary health care setting, outlining the minimum curriculum of the game (Textbox 1).

Periodic team meetings were scheduled during the design and development phases, to review each step, correct problems, and make decisions for the following stages, in an iterative process. The group agreed that the game should be developed in a way to satisfy 2 basic conditions: (1) to be educationally adequate, and (2) to be self-motivating and attractive to the final users.

The minimum curriculum describing teaching topics on insulin therapy selected for inclusion in the game.1. Goals of glycemic control in adults with DM2. When to start insulin in type 2 DM3. How to start insulin in type 2 DM (bedtime scheme)4. Recommendations on insulin use (storing, injection technique, and devices)5. Hypoglycemia: prevention, recognition, and treatment6. Self-monitoring of blood glucose7. Types of insulin: when to use which (NPH, regular)8. Oral antidiabetic drugs associated with insulin9. How to adjust insulin dosage10. How to intensify insulin therapy in type 2 DM (basal-plus scheme)11. How to start insulin in recent-onset severe type 2 DM (basal-bolus scheme)12. Type 1 DM: how to recognize it and how to start treatment13. How to recognize and manage diabetic ketoacidosis

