Also, this is the first known research trial studying the educational efficacy of a computer game in teaching PCPs about insulin therapy for DM. This is important, as most games for health care have not been validated as tools for education or health outcomes improvement, and there is a great need of good quality studies which can provide good scientific evidences to support the fast-growing field of games for health. Therefore, our study was designed to follow the rigorous guidelines for research on games´ effectiveness proposed by Kato [44].

We hope to demonstrate that a game can be an attractive and effective option for CME on insulin and diabetes. If we can do that, it would give more support to the idea that games can be very good options for large-scale CME, since they can be published on the Web to reach more health professionals compared to traditional learning activities, such as conferences or symposia, which cost substantial amount of time and money. A well-designed Web-based learning game can be used by the learners in their own time and rhythm, at possibly smaller costs, and have a number of significant potential advantages.

In conclusion, we demonstrated that the design and development of a game for education of PCPs on insulin management is possible with the collaboration of a multidisciplinary team. Although its efficacy still needs further evaluation, we think that InsuOnline can be a valuable tool for large-scale CME on DM, in view of its easy dissemination on the Web, customizable content, and accordance with adult learning principles. We hope it can contribute to improving PCPs´ knowledge and optimize DM control in primary care.

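### Group A enjoyment ratings are likely to come mainly from physicians who finish the game, because the only questionnaire named for non-finishers asks why they stopped

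*Protocol article*

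**What the plan says.** All the data collection at issue is described in the protocol article, section Educational Efficacy Assessment.

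- **Timing and content of the impression items.** "The participants will be asked a few Likert-scale and free text questions at the end of each intervention to assess their general impressions". Their purpose is given as "mostly to assess if it was pleasant or enjoyable".
- **What Group A must do to reach the end.** "They will be asked to play the game until its end, on the Web (with an individual login) in their own time and rhythm". Group B attends a single afternoon session.
- **What non-finishers are asked.** "For the participants in Group A that do not finish the game, the reasons for early withdrawal will be collected by an online questionnaire".
- **Other data that reach non-finishers.** "Software-recorded data on player´s usage of the game will be analyzed to assess the number of logins, time spent on the game, etc". There is also a general reminder rule: "We will contact (by phone or email) the participants who do not eventually fulfill the questionnaires at least twice".

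Attractiveness is a stated goal. The section Game Design lists it as the second of two basic conditions, "2) to be self-motivating and attractive to the final users", and the Discussion says "We hope to demonstrate that a game can be an attractive and effective option for CME on insulin and diabetes".

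**The concern.** The point at which enjoyment is measured may itself depend on enjoyment. A physician who finds the game dull or frustrating can simply stop logging in, and then never reaches the moment at which the items are due. The section Level Design adds to this: there are 16 patients, one per level, and a wrong choice means another attempt at the same level. Group B's single afternoon offers much less opportunity to leave out of dislike, so any such selection plausibly bears more on the game arm.

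At stake is the acceptability result. A high average rating could sit beside a sizeable share of abandoned games without reflecting the views of those who abandoned them. Ratings that were never collected cannot be recovered by a later analysis plan. Last observation carried forward does not help either, because enjoyment is measured once and there is no earlier value to carry.

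**Working it through.** **The plan's own figure.** The article states no figure for enjoyment. Its sample size (64 per group) concerns right answers on the knowledge test. It reproduces (63.77 per group by t test for a 0.5 SD difference, 80% power, two-sided 0.05, rounded up to 64) but has no bearing here.

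**Who is due which instrument, as written.**

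| Group A physician | Impression items | Withdrawal reasons | Usage logs |
|---|---|---|---|
| Finishes the game | Yes, at the end | Not applicable | Yes |
| Does not finish | Not stated | Yes | Yes |

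The cell marked as not stated is the gap. The article foresees non-finishers and plans to reach them with a form, but does not say that the form carries the rating items.

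**Formula.** Let q be the share of Group A starters who do not finish, and let F and Q be the ratings of finishers and quitters.

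- Rating for all starters = (1 − q) × F + q × Q
- Finishers-only rating minus all-starter rating = F − [(1 − q) × F + q × Q] = q × (F − Q)

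**Inputs.** Neither q nor F − Q is in the article, so both are assumptions. The central value q = 25% borrows the expected study dropout. That is a stand-in only, because a physician may quit the game and still answer every questionnaire. With 80 enrolled in Group A, 25% is 80 × 0.25 = 20 non-finishers and 60 finishers.

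**Overstatement of a mean Likert score, q × (F − Q), in points.**

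| q | Gap 0 | Gap 0.5 | Gap 1 | Gap 1.5 | Gap 2 |
|---|---|---|---|---|---|
| 10% | 0 | 0.05 | 0.10 | 0.15 | 0.20 |
| 25% | 0 | 0.125 | 0.25 | 0.375 | 0.50 |
| 40% | 0 | 0.20 | 0.40 | 0.60 | 0.80 |

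**The same as a percentage rating the game enjoyable.** Assume 80% among finishers.

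- q = 25%, quitters 30%: all starters 0.75 × 80 + 0.25 × 30 = 67.5%, so finishers-only is 12.5 points high.
- q = 20%, quitters 50%: 0.20 × (80 − 50) = 6 points high.
- q = 30%, quitters 20%: 0.30 × (80 − 20) = 18 points high.

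These three cases all assume a gap of 30 to 60 points, so the 6 to 18 point range excludes small biases by construction. It illustrates the mechanism and is not an estimate for this trial. The bias is zero if nobody quits, or if those who quit liked the game as much as those who finished, for example because they stopped for lack of time.

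**The case against.** The strongest reply is that the restriction to finishers is read into the text. The impression items go to participants in general, no sentence confines them to completers, and the reminder rule does not exclude either non-finishers or these items. This stands: a reader might infer that only finishers are ever asked, but the article does not say so. It does not remove the point, because the only stated trigger is the end of the intervention, and the reminder sentence does not say that a quitter is due the items.

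Second, the logs and the withdrawal reasons do cover non-finishers, and a dull game would show up there. This also stands, and it limits the harm. Neither source is a rating on the same scale, however, and the logs have no Group B counterpart, so they cannot correct the Likert result.

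Third, the trial's objective is educational efficacy. Enjoyment has no stated test, threshold or sample size, and no between-arm comparison of it is described. This stands. A reader might infer a planned comparison biased against Group B. The article supports only the narrower statement that the two ratings, if set side by side, may be selected differently. Group B physicians can also miss the session or leave early, so selection is not confined to Group A.

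Fourth, a journal article condenses, and the content of a short withdrawal form could sit in the full protocol. That is fair for the reporting denominator. It carries less weight for who is asked, because the article does specify both the timing of the items and the purpose of the non-finishers' form.

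**Conclusion.** The point holds in a limited form. As written, the plan most naturally yields Group A enjoyment ratings that come mainly from finishers, and these may be biased upward if physicians who stopped liked the game less. The direction depends on that condition, which is plausible but not established by the article.

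The size is unknown. Under the assumptions above it runs from 0.05 to 0.80 Likert points for 10–40% non-completion and gaps of 0.5 to 2 points, and it is zero with no gap. The article does not support saying that attractiveness will be judged from finishers alone, or that the result is certain to be inflated. The knowledge comparison is untouched. This is a worthwhile, inexpensive improvement to a secondary, descriptive measure of a stated design goal.

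**What to change.** 1. Add the same Likert items to the online withdrawal questionnaire already planned for Group A non-finishers.
2. Give the same items to any Group B physician who leaves the session early.
3. State that impressions are reported by arm for everyone who started the intervention, with the completion proportion beside the rating. A finishers-only rating can be shown as well, labelled as such.
4. Say that the existing rule of at least two contacts applies to these items, including for non-finishers.

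The cost is a few extra items on a form that is already being sent, plus a sentence on the denominator. Some quitters will not answer, so selection would be reduced but not necessarily removed, and the number responding by completion status should be shown. The resulting rating may be less favourable to the game.
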